## Abstract

**Background:**

Both acute normovolumic hemodilution (ANH) and autologous platelet-rich plasma (aPRP) have been demonstrated blood-protective effects in cardiac aortic surgery; however, the efficacies of the two methods have not been compared. This study aims to compare the effects of aPRP and ANH prior to aortic surgery on postoperative bleed and other outcomes.

**Methods and analysis:**

This is a prospective, single-center, double-blind controlled clinical trial including 160 patients randomized 1:1 to receive aPRP (test group) or autologous whole blood (ANH, control group). The primary objective is to compare the drainage volumes in the two groups at 24, 48, and 72 h postoperatively. Secondary outcomes include input of allogeneic blood and blood products and durations of aortic block, extracorporeal circulation, deep hypothermic arrest of circulation, tracheal extubation, hospital stay, requirement for secondary surgical hemostasis, and application of intra-aortic balloon pump or extracorporeal membrane oxygenation in the two groups. In addition, heart rate, systolic blood pressure, diastolic blood pressure, central venous pressure, and thromboelastography recorded before blood reservation (T1), after blood reservation (T2), before blood transfusion (T3), and after the blood is returned (T4) to the transfusion will be compared between the two groups of patients.

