
ANH is a common clinical practice for blood conservation during autologous blood transfusion and has been used in a variety of procedures. ANH has been shown to reduce the use of postoperative blood products, drainage, and the rate of secondary open-heart hemostasis in patients undergoing cardiac surgery [10]. Blood separation has been shown to have a similar effect [11]. However, there is currently a lack of randomized controlled trials, and it has been suggested that its use should be limited to aortic surgery, with further information needed regarding its use during cardiac surgery.

Although some studies have confirmed the hemoprotective effects of ANH and blood separation in aortic surgery, no randomized controlled trials have compared these two methods. We designed a study to test the hypothesis that blood separation techniques may be more effective for restoring coagulation and reducing the need for allogeneic blood products.

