## Methods

### Study design {8}

This is a prospective, single-center, double-blind controlled clinical trial comparing the use of autologous platelet-rich plasma (aPRP, experimental group) and autologous whole blood (ANH, control group) in patients undergoing aortic surgery. The main study objectives include the volumes of allogeneic blood and blood products needed. We also aim to compare the durations to aortic block, extracorporeal circulation, deep hypothermic arrest of circulation, and tracheal extubation, length of hospital stay, and the incidence and mortality of secondary surgical hemostasis or application of intra-aortic balloon pump (IABP) and extracorporeal membrane oxygenation (ECMO) in both groups. Heart rate, systolic blood pressure, diastolic blood pressure, central venous pressure, and thromboelastography (TEG) were also compared before blood reservation (T1), after blood reservation (T2), before blood reserving (T3), and after (T4) blood reserving.

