### Determination of sample size

We calculate the required sample size based on the drainage volume (mean ± standard deviation) at 24 h after the end of the manual procedure. Our preliminary study showed that the drainage volumes at 24 h postoperatively in the aPRP and control groups were 316 ± 102 and 378 ± 133 mL, respectively. Eighty patients per group were therefore needed to detect a difference with a power of 80% and a type I error rate of 5% using the PASS software.

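### The article contradicts itself on whether allogeneic blood use is a primary or a secondary outcome, and names three drainage times as primary without saying which one decides

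*Protocol article*

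**What the plan says.** The Methods and analysis part of the abstract reads: "The primary objective is to compare the drainage volumes in the two groups at 24, 48, and 72 h postoperatively". It then ranks transfusion below drainage: "Secondary outcomes include input of allogeneic blood and blood products".

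Study design {8} orders them differently: "The main study objectives include the volumes of allogeneic blood and blood products needed". Drainage volume does not appear in that section.

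The hypothesis at the end of the Background is that "blood separation techniques may be more effective for restoring coagulation and reducing the need for allogeneic blood products". It does not mention drainage either.

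Determination of sample size uses one drainage time: "We calculate the required sample size based on the drainage volume (mean ± standard deviation) at 24 h". The pilot volumes "in the aPRP and control groups were 316 ± 102 and 378 ± 133 mL, respectively", and the section gives 80% power, 5% type I error and 80 patients per group.

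Statistical analysis plans a t-test or Mann–Whitney test for continuous variables. It mentions a repeated-measures ANCOVA only as an option that might work better when normality fails. It does not identify the primary comparison. Subgroup analyses {20b} would confine any subgroup work to the main result, without saying what that is.

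**The concern.** Allogeneic blood use is secondary in one section and a main objective in another, and the two rankings cannot both hold. The set that the abstract calls primary is also not reduced to one deciding comparison: it has three times, while the trial is sized on one.

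A trial's main claim depends on a primary outcome fixed before the data are seen. If the article leaves it open, the result presented as primary could be chosen afterwards among 24, 48 and 72 h drainage and transfusion volume. The stated 5% error and the sample size were set for 24 h drainage and do not carry over to a choice of that kind.

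**Working it through.** **1. The sections side by side**

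| Section | Drainage | Allogeneic blood |
|---|---|---|
| Abstract, Methods and analysis | Primary, at 24, 48 and 72 h | Secondary |
| Background (hypothesis) | Not mentioned | Named, with coagulation |
| Study design {8} | Not mentioned | Among the main objectives |
| Determination of sample size | 24 h only | Not mentioned |

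The direct conflict is between the abstract and Study design. The sample size section does not call 24 h drainage the primary outcome; it uses one member of the abstract's set.

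**2. The plan's own figure**

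Inputs from Determination of sample size: means 316 and 378 mL, SDs 102 and 133 mL, 5% error, 80% power. Sidedness is not stated; two-sided is assumed.

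- Difference: 378 − 316 = 62 mL.
- Common SD: √[(102² + 133²)/2] = √14046.5 = 118.5 mL.
- Standardised difference: 62/118.5 = 0.523.
- n per group = 2(1.960 + 0.842)²/0.523² ≈ 57.4, so 58 (59 with the t distribution).

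The stated 80 per group is not reproduced. At 80 per group, power = Φ(0.523 × √(80/2) − 1.960) = Φ(1.349) = 91% (90.8% with the t distribution). That mismatch is a separate matter. It is noted here because the power figures below depend on it.

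**3. Error if any one drainage time could count as success**

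Each time is tested at two-sided 5%. If the tests were independent, the chance of at least one false positive is 1 − 0.95³ = 14.3%. For correlated tests, 1,000,000 draws from a three-variable normal distribution with common correlation ρ, counting any |Z| > 1.96, gave:

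| ρ | 0 | 0.5 | 0.7 | 0.8 | 0.9 | 0.95 |
|---|---|---|---|---|---|---|
| At least one false positive | 14.3% | 12.5% | 10.9% | 9.8% | 8.3% | 7.4% |

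Counting only results that favour aPRP (nominal 2.5%), the figure is 7.3% if independent and 4.2% at ρ = 0.9.

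**4. Error if one allogeneic volume counted as well**

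Four independent tests give 1 − 0.95⁴ = 18.5%. With drainage correlations of 0.5 to 0.95 and drainage–transfusion correlations of 0 to 0.7, the simulated range is 10.2% to 17.0%.

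**5. Power if all three drainage times stay primary**

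Bonferroni level: 0.05/3 = 0.0167, critical value 2.394. Power for 24 h drainage at 80 per group = Φ(3.309 − 2.394) = Φ(0.915) = 82% (81% with the t distribution). No planning figures are given for 48 h, 72 h or transfusion, so power there cannot be checked.

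**The case against.** The best defence is that drainage is clearly intended. The abstract's background and discussion speak of postoperative bleeding, the Follow-up section has drainage recorded daily on days 1 to 3, and the sample size uses drainage. The Study design sentence is plural and open-ended, so it need not exclude drainage, and a background hypothesis does not define an outcome. This makes drainage the more likely intention. It does not remove the conflict, because the one item that Study design does name is the item that the abstract ranks as secondary. Nor does it say which of the three times decides.

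A second defence is that an alpha split, a testing order or a success rule commonly sits in the statistical analysis plan, which is not shown. That stands: the absence of such a rule here is not the finding. The contradictory ranking is in this article, however, and has to be corrected here.

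Two stronger readings are tempting, and the article supports neither. A reader might infer three incompatible primary outcomes, but 24 h drainage belongs to the abstract's set and is a narrower choice within it. A reader might also infer that the plan allows success on any one result at well above 5% error. No section says that any single result suffices, the correlations are not given, and the number of blood product comparisons is not defined. If the drainage times are highly correlated, the inflation from drainage alone is modest.

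The optional repeated-measures model might seem to combine the times, but it is tied to non-normality and is not fixed as the primary test. Nor can 80 per group be read as a hidden correction for three tests. Bonferroni over three would need 77 (78 with the t distribution), which is close, but the section describes one comparison at 5%.

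**Conclusion.** The point holds as an inconsistency within the article. Allogeneic blood use is secondary in the abstract and a main objective in Study design, and three drainage times are primary with none marked as decisive although the trial is sized on one. Confidence in this is high, because it rests on the text alone.

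The size is conditional. If any of the three drainage times counted as success, the false-positive chance would be about 7% to 14%; with one allogeneic volume added, about 10% to 19%. Both ranges assume two-sided 5% tests, an any-one-suffices rule that the article does not state, and correlations that it does not give. They measure what an unfixed primary outcome could cost and are not the error rate of a stated rule.

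**What to change.** Before the first-level unblinding, name 24 h drainage as the single primary outcome at two-sided 5%, in the same words in the abstract, Study design, Determination of sample size and Statistical analysis. Rank 48 h and 72 h drainage and allogeneic blood volumes as secondary, and align the hypothesis in the Background. This choice matches the only planning figures given.

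If the sponsor prefers to keep all three times primary, the error must be controlled across them. One option is to test each at 0.0167, which costs no patients for the 24 h test on the stated figures. Another is one joint repeated-measures test, prespecified as the primary analysis and not left as an option.

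The cost is a protocol modification with stated reasons and ethics committee approval, as Important protocol modifications {25} requires. No extra patients or data are needed. The downside of a single primary outcome is that the 48 h, 72 h and transfusion results could no longer carry the main claim on their own.

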**Discussion:**

This study will demonstrate if the use of aPRP could reduce the risk of bleeding after aortic surgery compared with ANH. The results are expected to have practical clinical applications in terms of more effective blood protection and shorter hospital stay.

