#### Inclusion and exclusion criteria

The inclusion criteria are patients undergoing aortic revascularization under deep hypothermic arrest circulation in an elective or emergency setting, and patients and families provided informed consent. The exclusion criteria are a history of previous cardiac surgery, preoperative hemoglobin < 90 gL, hematocrit < 30%, platelets < 100 × 10^9^L, and cardiac insufficiency, left ventricular ejection fraction < 50%, patients who died following surgery for a variety of reasons (hemorrhagic shock, heart failure, infection, etc.), or severe aortic stenosis. The discharge criteria are good recovery of cardiac function, hemodynamic stability maintained, and blood counts and other biochemical parameters are normalized.

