### Statistical analysis

Statistical analysis will be carried out using the SPSS software, version 26.0 for Windows (SPSS, Inc., Chicago, IL, USA). Continuous variables will be described as mean (standard deviation) or median (25% and 75% percentiles) and analyzed using independent *t*-tests or Mann–Whitney *U* tests, respectively. Categorical variables will be described as a frequency or percentage and analyzed by *χ*^2^ tests. Prior to statistical analysis, each continuous variable will be analyzed to determine if it is normally distributed. If the assumption of a normal distribution is violated, the appropriate transformation will be used, and analysis using repeated measures analysis of covariance (ANCOVA) models may be more effective.

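### Extubation time and hospital stay are compared as plain durations while post-surgery deaths are excluded, so the comparison covers survivors only, and no rule covers deaths if they are kept

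*Protocol article*

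**What the plan says.** The abstract names as secondary outcomes "durations of aortic block, extracorporeal circulation, deep hypothermic arrest of circulation, tracheal extubation, hospital stay". Study design {8} repeats them and places a mortality comparison in the same sentence: "tracheal extubation, length of hospital stay, and the incidence and mortality of secondary surgical hemostasis".

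The Statistical analysis section treats all continuous variables alike. They are summarised by mean or median and "analyzed using independent *t*-tests or Mann–Whitney *U* tests, respectively". If normality fails, it allows a transformation or repeated-measures ANCOVA. It gives no method for a duration that death can cut short.

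Deaths are mentioned under Inclusion and exclusion criteria, where the exclusions include "patients who died following surgery for a variety of reasons (hemorrhagic shock, heart failure, infection, etc.), or severe aortic stenosis". The same section defines the ordinary end of the stay by recovery: "The discharge criteria are good recovery of cardiac function, hemodynamic stability maintained".

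The abstract's Discussion says the results should have practical use in terms of "more effective blood protection and shorter hospital stay".

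**The concern.** Extubation and discharge alive are events that death can prevent. A t-test or Mann–Whitney test on the recorded durations needs a number for every patient analysed, so the answer depends on what is done with patients who die first.

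The protocol's one statement on this removes them. Death after surgery occurs after randomisation and is an outcome, so excluding on it leaves groups that randomisation did not form. If the patients who die would otherwise have had the longest stays, the arm that loses more of them keeps the healthier survivors and shows the shorter stay.

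Reversing that exclusion without adding a rule does not solve the problem. A death on day 3 could then be entered as a 3-day stay, among the best values in the data, and a patient who dies intubated still has no extubation time.

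At stake is the meaning of one of the two practical benefits the trial expects to report: a shorter stay could partly reflect more deaths.

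**Working it through.** **1. The sections side by side.**
- Inclusion and exclusion criteria: deaths after surgery leave the trial. Stay and extubation time are then known only for survivors.
- Study design {8}: mortality is compared between arms. That needs the deaths to stay in, so the two sections conflict.
- Statistical analysis: the same two tests apply in either case, with no value or rank assigned to a death.
- The treatment of non-adherence and missing data {20c}: replacement of missing values is optional and unspecified, and death is not mentioned.

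**2. Inputs.** From the protocol: 80 patients per group, 1:1 allocation, Mann–Whitney test. I assumed a two-sided 5% level. The protocol gives no mortality, length of stay or time to death, so there is no figure of its own to reproduce. The rest is assumed:
- mortality 5% v 5%, 5% v 10% and 5% v 15% (of 80 patients: 4, 8 and 12 expected deaths);
- the stay a patient would have had is lognormal, median 14 days, log-SD 0.4, identical in both arms;
- time to death is lognormal, median 4 days, log-SD 0.5;
- correlation between underlying stay and liability to die is 0 or 0.7.

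**3. Shift in mean stay, by formula.**

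*Deaths kept as short stays, correlation 0.* Mean stay is 14 × exp(0.4²/2) = 15.17 days. Mean time to death is 4 × exp(0.5²/2) = 4.53 days. Each extra percentage point of deaths lowers the arm's mean by 0.01 × (15.17 − 4.53) = 0.106 day.
- 5% v 10%: 5 × 0.106 = 0.53 day shorter in the worse arm.
- 5% v 15%: 10 × 0.106 = 1.06 days shorter.

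*Deaths dropped, correlation 0.7.* The survivors' mean is 15.17 × Φ(c − 0.7 × 0.4)/Φ(c), with Φ(c) = 1 − mortality.
- 5%: 15.17 × 0.9139/0.95 = 14.59 days.
- 10%: 15.17 × 0.8417/0.90 = 14.18 days, a gap of 0.4 day.
- 15%: 15.17 × 0.7753/0.85 = 13.83 days, a gap of 0.76 day.

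*Deaths dropped, correlation 0.* The survivors' mean is 15.17 days in both arms, a gap of 0.

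**4. How often the worse arm is significantly favoured.** Simulation, 10,000 trials per cell, Mann–Whitney at two-sided 5%. The chance level in one direction is 2.5%.

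| Handling of deaths | Correlation | 5% v 5% | 5% v 10% | 5% v 15% |
|---|---|---|---|---|
| Dropped | 0 | 2.4% | 2.4% | 2.5% |
| Dropped | 0.7 | 2.4% | 5.6% | 10.5% |
| Kept as short stays | 0 | 2.6% | 7.4% | 17.9% |
| Ranked worst | 0 | 2.4% | 0.7% | 0.2% |
| Ranked worst | 0.7 | 2.4% | 1.4% | 0.6% |

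Separate runs of 4,000 trials agree within simulation error: about 5% and 10% for deaths dropped with correlation 0.7, and about 7% and 17% for deaths kept with correlation 0. A wider spread of stays (log-SD 0.5) also gives 10% for deaths dropped at 5% v 15%.

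Extubation time was not simulated. A patient who dies intubated has no value under either handling, so the same selection of survivors applies.

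**The case against.** The strongest reply has four parts.

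*The plan does not score death as a fast recovery.* This stands. A reader might infer from the Statistical analysis section that a patient who dies on day 3 contributes a 3-day stay. The documents do not say so: that section is silent on death, the exclusion criteria remove these patients, and the discharge criteria suggest that stay ends at recovery. The figures for deaths kept as short stays apply only if the exclusion is not carried out and no other rule replaces it.

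*Under the rule actually written there may be no bias.* This stands in part. With deaths dropped and death unrelated to the stay the patient would have had, the test keeps its nominal level. Bias appears only if sicker patients die more often and the arms differ in deaths. The causes of death the protocol lists (shock, heart failure, infection) make the first condition plausible, but the correlation of 0.7 is an assumption.

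*The mortality gaps are hypothetical.* This stands. Nothing in the protocol suggests a two- or three-fold difference between the two techniques, and with equal mortality no handling shows a bias.

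*Conventions for death are commonly left to the analysis plan.* This would answer a complaint about missing detail alone. It does not answer an article that itself fixes the tests, excludes deaths after randomisation and also announces a mortality comparison.

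**Conclusion.** The point holds in limited form. Read literally, the protocol compares extubation time and stay in survivors only. Read so that mortality can be compared, it has no rule for deaths in these two durations. Under either reading the arm with more deaths can look better.

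The size is conditional. At assumed mortality of 5% v 10% and 5% v 15%, with no true effect on stay, the worse arm is significantly favoured in about 5–6% and 10% of trials with deaths dropped and a severity–death correlation of 0.7. With deaths kept as short stays and no correlation, the figures are about 7% and 17–18%. Ranking death worst brings this below 1.5%, against 2.5% by chance. The direction is more secure than the numbers.

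It would go too far to infer that a shorter stay in this trial would be an artefact of mortality: the documents give no mortality rate and no reason to expect the arms to differ. The primary drainage outcome and its sample size are not touched by the choice of method for these durations. This is a should-fix companion to correcting the exclusion of deaths.

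**What to change.** The changes belong together. Asking for all randomised patients while deaths remain an exclusion would create a new contradiction.

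1. Remove death after surgery from the exclusion criteria, keep all randomised patients in the comparison, and report mortality by arm.
2. Add to Statistical analysis, for example: *For extubation time and hospital stay, a patient who dies before the event is given the worst rank, and the arms are compared by Mann–Whitney test in all randomised patients. The cumulative incidence of extubation and of discharge alive is shown by arm, with death as a competing event. Durations in survivors are given as description only.*
3. State that any conclusion about a shorter stay rests on the ranked comparison, read beside mortality.

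Cost: a few sentences, and dates of extubation, discharge and death, which the hospital record should already hold. The Mann–Whitney test is already in the plan, and sample size and treatment do not change. The drawback is that the result is read in ranks or cumulative incidence instead of mean days.

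### TEG after return of the autologous product should be compared by ANCOVA on the pre-collection value; the plan ties its only covariate-adjusted model to non-normality

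*Protocol article*

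**What the plan says.** The Background closes with the hypothesis that "blood separation techniques may be more effective for restoring coagulation and reducing the need for allogeneic blood products". Use of allogeneic products is a listed outcome. For coagulation itself, the only assay named is TEG.

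In the Abstract (Methods and analysis), drainage is the primary objective: "The primary objective is to compare the drainage volumes in the two groups at 24, 48, and 72 h postoperatively". A list of secondary outcomes follows, then a third group: "In addition, heart rate, systolic blood pressure, diastolic blood pressure, central venous pressure, and thromboelastography recorded" at four times. The Abstract gives those times, and the plan to contrast the arms at each of them, as "before blood reservation (T1), after blood reservation (T2), before blood transfusion (T3), and after the blood is returned (T4) to the transfusion will be compared".

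Data collection and management gives the same TEG schedule: before and after collection, and before and after the return infusion. It adds that TEG results will guide the use of fibrinogen, prothrombin complex, coagulation factors and platelets. Study design {8} words the last two times differently: "before blood reserving (T3), and after (T4) blood reserving".

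Under Statistical analysis, continuous variables are "analyzed using independent *t*-tests or Mann–Whitney *U* tests, respectively". If normality is violated, a transformation is to be used, and repeated-measures ANCOVA is mentioned as something that may work better. No other covariate-adjusted or longitudinal model appears.

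**The concern.** The four times do not carry the same information about restored coagulation. T1 precedes any study procedure, so under randomisation a difference there is chance. T2 and T3 precede the return of blood or plasma and describe what collection and bypass have done. Only T4 can show an effect of giving the product back. The stated analysis nevertheless compares the arms in the same way at every time and does not connect T4 to T1.

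The trigger for the better model is also misplaced. Non-normality is a reason to transform, or to use a rank or robust method. The reason for ANCOVA is a baseline measurement that predicts the outcome, and that holds whether or not the data look normal. As written, TEG values that pass the normality check get the less precise analysis, with no protection against a chance T1 imbalance.

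At stake is how precise and how readable the coagulation result is. The primary drainage comparison is not affected.

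**Working it through.** **Inputs.** From the document: 80 patients per group (Determination of sample size, where it is set for 24 h drainage), four TEG times, and unadjusted two-group tests. The document gives no TEG effect size, standard deviation or T1–T4 correlation and no TEG sample size, so there is no TEG figure to reproduce. Assumed: two-sided 5% tests and a T1–T4 correlation r of 0.3, 0.5 or 0.7.

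**Step 1: precision from adjusting T4 for T1.** With a linear baseline covariate, the variance of the group difference is multiplied by 1 − r². The equivalent unadjusted size per group is 80 / (1 − r²).

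| r | 1 − r² | variance cut | equivalent n per group |
|---|---|---|---|
| 0.3 | 0.91 | 9% | 80/0.91 = 88 |
| 0.5 | 0.75 | 25% | 80/0.75 = 107 |
| 0.7 | 0.51 | 49% | 80/0.51 = 157 |

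The last row needs care: the multiplier is 0.51, so the cut is 1 − 0.51 = 49%. The range of the reduction is therefore r² = 9% to 49%.

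**Step 2: what a chance T1 imbalance does to the unadjusted T4 test.** With no true effect, and given a T1 statistic of z = 1.96, the T4 statistic is normal with mean 1.96r and variance 1 − r². The conditional rejection probability is P(Z > (1.96 − 1.96r)/√(1 − r²)) + P(Z < (−1.96 − 1.96r)/√(1 − r²)).

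- r = 0.3: 0.0752 + 0.0038 = 0.079
- r = 0.5: 0.1289 + 0.0003 = 0.129
- r = 0.7: 0.2052 + 0.0000 = 0.205

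These rates apply to one unlucky imbalance. Over all randomisations the unadjusted T4 test rejects at its nominal 5%.

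**Step 3: if any significant TEG time were claimed.** For one TEG parameter tested at four times with no true effect, independent tests would give 1 − 0.95⁴ = 18.5%. With equal correlation between times, numerical integration gives 17.4%, 15.6% and 13.0% at correlations of 0.3, 0.5 and 0.7. The figure is therefore about 13–17%, and it applies only if a difference at any time, T1 included, were presented as evidence.

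**Step 4: the time labels side by side.** The Abstract places T3 before transfusion and T4 after the blood is returned. Data collection and management has the same two moments around the return infusion. Study design {8} puts both around blood reserving, which repeats T1 and T2. Two of the three places agree, so the intended timing can be recovered, but the Methods definition of T4 is wrong as it stands.

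**The case against.** **The unadjusted T4 comparison is valid.** This is correct. Randomisation protects its unconditional error rate, and the 8–21% in step 2 is conditional on a selected imbalance. The argument for adjustment is precision and protection against bad luck.

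**The analysis plan is not shown and may settle the details.** This also stands for naming the TEG parameter, labelling analyses as exploratory and handling multiplicity, so none of these is part of the point. It does not excuse the misplaced trigger, which is in the text that is shown.

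**TEG is a supportive measure.** It comes after the primary and secondary outcomes, and it also guides treatment, so measuring it four times does not imply four efficacy claims. That limits how much the point matters, but coagulation is still half of the stated hypothesis.

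**T4 does not isolate the returned product.** This stands. Blood products given on TEG results may also move T4. ANCOVA on T1 does not remove that, and the report must say so.

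**A stronger reading is tempting:** that five variables at four times amount to 20 tests, each at full alpha, with a 42–61% chance of a false positive under assumed correlations. The document does not support it. Its only stated type I error rate belongs to the 24 h drainage sample size, and testing TEG at full alpha is an inference from silence. The Abstract does rank its outcomes, and hospital stay is listed as secondary. Four of the five variables are hemodynamic and cannot support a coagulation claim.

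**Conclusion.** The point holds as a fault in the stated analysis. The plan collects a pre-intervention TEG value, assigns tests that ignore it, and makes the one model that could use it depend on non-normality. Adjusting T4 for T1 would cut the variance of the T4 comparison by 9% to 49% for assumed correlations of 0.3 to 0.7, equivalent to about 88 to 157 unadjusted patients per group instead of 80. The document gives no correlation, so the true gain within or outside that range is unknown.

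A reader might infer that the planned T4 test is biased or that the trial's main claim has an inflated error rate. Neither follows. The T4 test keeps its nominal error rate, and the relevant multiplicity figure is about 13–17% for one TEG parameter, only if any significant time were claimed. The T3/T4 label conflict is real but minor.

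**What to change.** In Statistical analysis, state that:

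- the between-group difference in TEG at T4 is estimated by ANCOVA with the T1 value as covariate, with a 95% confidence interval, regardless of the normality check and with the outcome transformed if needed;
- T1 is reported descriptively and not tested;
- T2 and T3 are presented as describing collection and bypass;
- T4 may also reflect blood products given on TEG results, and is interpreted with that in mind.

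In Study design {8}, reconcile the T3 and T4 labels with the Abstract and with Data collection and management.

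The cost is a few sentences before unblinding. No new data are needed, because TEG is already recorded at all four times. The one thing given up is the use of T1–T3 differences as evidence of restored coagulation.
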